### 9.4.3 Reporting of Adverse Events

All serious adverse events and new Grade 3 or 4 toxicities reported by the subject or detected and reported to any study physician will be classified as above and recorded on an Adverse Event Form and in the source document. The causal relationship will be evaluated by the Principal Investigator and the relationship of the event to the study drug will be reported to the IRBs and the chair of the DSMB within 72 hours and to the NIH and FDA.

Other adverse events will be summarized approximately quarterly for the DSMB and the IRB.

## 9.5 Withdrawal of Subjects

The study drug will be discontinued and the subject withdrawn from the study if any of the following occur:

- An adverse event, intercurrent illness, or other medical condition or situation occurs such that continued participation in the study would not be in the best interest of the subject
- If an enrolled subject begins immunosuppressive medication or events occur which raise questions as to the safety of continued administration of LGG, and/or the subject's primary care physician wishes to withdraw the subject from the study
- Grade 3 or Grade 4 gastrointestinal side effects
- *Lactobacillus* bacteremia or invasive *Lactobacillus* infection
- Subject withdraws consent
- Subject is lost to follow-up

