## 7.4 Early Termination Visit

Subjects are free to withdraw from participating in the study at any time upon request. The reason for withdrawal will be documented on the CRF. If a subject withdraws early due to an adverse event, he/she will be followed until resolution/stabilization of the adverse event. Subjects will be withdrawn if they are hospitalized.

If a subject prematurely withdraws from the study or is withdrawn from the study, the same procedures and evaluations will be performed as in the final study visit if possible at the time of withdrawal from the study (i.e. study subject withdraws at time of a visit and consents to having procedures/evaluations done):

- Interval medical history, concomitant therapy/medications, consumption of probiotics, yogurt, etc and adverse event questionnaire, self report and diary review
- Physical exam with weight and vital signs
- Routine Laboratory tests
  - CBC
  - Serum chemistries/liver function tests
- Research Laboratory tests
  - Collection of nasopharyngeal specimens for microbiota
  - Collection of stool sample for microbiota and LGG culture
  - Sub-study only – blood for DNA, mRNA and cytokines

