#### **9.4.2 Recording of Adverse Events**

Each adverse event will be recorded on an Adverse Event Case Report Form which will include the following information:

- Description of symptoms and/or event
- Onset and Duration, including intermittent or not
- Adverse Event Severity (including determination if the event qualifies as a Serious Adverse Event – see Section 9.4.2.1 below)
- Assessment of relationship between the study drug and adverse event (see Section 9.4.2.2 below)
- Action(s) taken to treat the adverse event
- Outcome

Once identified, all AEs (including serious) will be followed until resolved or until the PI considers that the subject is stable. Evaluation of AEs will be done during follow-up visits, as well as during unscheduled visits, and scheduled telephone calls. All communications, examinations, and testing that occurs as a result of the AE will be clearly documented on AE forms and the appropriate CRFs. Changes in the severity of an AE will be documented to allow an assessment of the duration of the event at each level of intensity to be performed.

If events occur which raise questions about the safety of continued administration of LGG, the subject's physician will have the option to withdraw the subject from the study.

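### The events that stop study drug also end study participation, so scheduled surveillance for new events stops in subjects withdrawn for safety reasons

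*Protocol*

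**What the plan says.** Section 9.5 joins two decisions in one sentence: "The study drug will be discontinued and the subject withdrawn from the study if any of the following occur". The list under it includes "Grade 3 or Grade 4 gastrointestinal side effects", Lactobacillus "bacteremia or invasive *Lactobacillus* infection", and an adverse event, illness or other situation that makes staying in the study contrary to the subject's best interest. Withdrawal of consent and loss to follow-up stand in the same list. Section 7.4 adds, without regard to cause: "Subjects will be withdrawn if they are hospitalized".

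Some follow-up survives withdrawal:

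- Section 7.4: "If a subject withdraws early due to an adverse event, he/she will be followed until resolution/stabilization of the adverse event".
- Section 9.4.2: "all AEs (including serious) will be followed until resolved or until the PI considers that the subject is stable".
- Section 9.6: after treatment for invasive disease, throat and stool are cultured and the subject is followed until LGG can no longer be recovered.
- Section 7.4 on early termination: "the same procedures and evaluations will be performed as in the final study visit if possible at the time of withdrawal from the study". The text explains this as a subject who withdraws at a visit and agrees to the procedures.

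No section describes a subject who stops LGG but stays on the Day 28 and Day 56 schedule.

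**The concern.** The sole primary objective is safety and tolerability, and several withdrawal triggers are themselves safety outcomes. Whether a subject goes on being observed for new events therefore depends on what has already happened to that subject, so the loss is informative. The events that could be missed are later or additional toxicities, laboratory changes at Day 28 and Day 56, and persistence of LGG in stool outside invasive disease. Observation after dosing is not redundant for a live organism: Section 2.1.7.1 concludes that colonisation can outlast dosing by a month or more. Section 2.1.10 makes completion of this stage and FDA approval a condition for starting the next stage in elderly subjects.

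**Working it through.** The protocol gives no power or precision figure to reproduce. Section 11.1 takes the 10-15 subjects from an FDA recommendation. The check sets the text side by side and then sizes the loss.

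**Text against text**

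| Place | What it requires |
|---|---|
| 9.5 and 7.4 | Triggered subjects leave the study |
| 9.4.1 | Monitoring for events from enrollment for at most 2 months |
| 4 | DSMB report with safety data on every subject to Day 56 |
| 4, 7.2, 7.3 | Calls on Days 3, 7 and 14; visits on Days 28 and 56 with laboratory tests, questionnaire, diary review and stool culture |
| 11.3.1 | Adverse events summarised for everyone with at least one dose |

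Section 9.4.1 states a maximum, so read alone it tolerates an early end. Section 4 does not: for a withdrawn subject its report can hold only what event follow-up and a conditional withdrawal assessment happen to supply.

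**Share of the cohort** = withdrawals / N, with N = 10 to 15:

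- One withdrawal: 1/15 = 6.7% to 1/10 = 10%.
- Two withdrawals: 2/15 = 13.3% to 2/10 = 20%.

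**Scheduled days lost** = 56 - t, for withdrawal on Day t:

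- Day 3: 53/56 = 95%.
- Day 7: 49/56 = 88%, with the Day 14 call and both follow-up visits.
- Day 14: 42/56 = 75%.
- Day 28: 28/56 = 50%.

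An early-termination assessment, if done, recovers one early set of laboratory tests and samples. It does not replace the Day 28 or Day 56 set.

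**Effect on precision for a later event never observed.** The one-sided 95% upper bound for 0 events in m subjects is 1 - 0.05^(1/m):

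- N = 10: 25.9% with all observed, 28.3% with nine.
- N = 15: 18.1% with all observed, 19.3% with fourteen.

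**Chance that the rule bites at all** = 1 - (1 - p)^N. The protocol gives no trigger rate, so p is an assumption:

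| p per subject | N = 10 | N = 15 |
|---|---|---|
| 2% | 18% | 26% |
| 5% | 40% | 54% |
| 10% | 65% | 79% |

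**Where bias can arise.** Section 3.2.1 counts a new Grade II-IV toxicity possibly or probably related to LGG. If the trigger is such an event, it is recorded and the subject already counts, so lost visits cannot undo that. If the trigger is not such an event, for example an unrelated hospitalisation, the subject may have no primary event when observation stops, and a later one may go unseen. Second or later events can be missed in either case.

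**The case against.** The strongest reply is that the worst related outcomes are the best documented. Serious events and new Grade 3 or 4 toxicities go to the IRBs and the DSMB chair within 72 hours (9.4.3). A Grade 4 or serious event judged probably or definitely related suspends the study (9.7). The subject remains in the at-least-one-dose summary (11.3.1). The upper bounds move only modestly when one subject is lost, and the trial is descriptive. All of this stands, and it limits the severity.

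Four stronger readings are tempting but not supported:

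- **That follow-up ends altogether, or covers only the triggering event.** Section 9.4.2 follows every adverse event already identified. Only scheduled surveillance for new ones lapses.
- **That LGG persistence goes unrecorded in all these subjects.** Section 9.6 keeps cultures going in invasive disease.
- **That any adverse event removes a subject.** Section 9.5 limits this ground to events that make participation contrary to the subject's interest.
- **That 7.4 and 9.5 flatly contradict each other on hospitalisation.** Section 9.5 omits it by name, but does not call its list complete and includes intercurrent illness. The lists need reconciling; neither denies the other.

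Nor can one assume that a hospitalised subject never has the early-termination assessment. It may well be missed, but the text makes it conditional and does not exclude it.

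**Conclusion.** The point holds, at moderate severity. Followed as written, Sections 9.5 and 7.4 end scheduled surveillance for reasons that are often safety outcomes, and this is not reconciled with Sections 4 and 9.4.1. A reader might infer that the whole safety summary is tilted toward LGG looking safe. The protocol does not support that, because a related Grade 3 or 4 trigger is already counted in the primary outcome. The possible bias is confined to second or later events and to withdrawals whose trigger was not a primary-outcome event.

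The cohort shares and days lost follow from the stated N and schedule. The Day 7 case is illustrative and is a maximum, since an early-termination assessment would recover part of it. The chance of any such withdrawal rests wholly on the assumed trigger rates.

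**What to change.** In Sections 7.4 and 9.5, state separately what ends study drug and what ends data collection. Reconcile the two trigger lists, including where hospitalisation belongs, without changing the drug-stopping criteria. Then provide that a dosed subject who stops the drug remains in follow-up for the Day 28 and Day 56 safety assessments, by telephone if a visit is not possible. The exceptions are withdrawn consent, lost contact, or a judgement by the investigator or the subject's physician that further study assessments are not in the subject's interest. The last exception preserves the best-interest and physician-withdrawal grounds already in Sections 9.4.2 and 9.5.

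The cost is a short amendment that needs IRB review (14.2). The visits are already planned, with a few extra calls at most. Some assessments will be incomplete, since a telephone contact yields no laboratory tests or cultures; these gaps can be described under the missing-data provision in Section 11.3.1.

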## 9.6 Rescue Medication

There is a theoretical risk of translocation of LGG across the bowel wall and resultant clinical infection caused by *Lactobacillus*. Possible infections include bacteremia, endocarditis, or abscesses. The antibiotic susceptibilities of LGG, as reported by various researchers, are attached (Appendix C). Based on the available literature, including experimental models of infective endocarditis with *Lactobacillus plantarum*, we would recommend treatment of *Lactobacillus* endocarditis with a beta-lactam and gentamicin, but bacteremia alone or other sites of infection may be treatable with a beta lactam only. If any study subject develops invasive disease

(bacteremia, endocarditis, etc.), we will recommend this treatment course, but will also ask that an independent infectious disease physician (not involved in the study) evaluate and treat the subject. We will also obtain *in vitro* sensitivity data on the specific isolate as several articles show a benefit of treating with antibiotics to which the organism is sensitive *in vitro*.

The dose, route, frequency, and duration of treatment will be determined by the infectious disease consultant caring for the subject but the recommended regimens are as follows:

Ampicillin 2 grams intravenously every 6 hours (or alternative beta-lactam antibiotic) for 14 days  
or  
Clindamycin 900 mg intravenously every 8 hours for 14 days or  
Moxifloxacin 400 mg intravenously every 24 hours for 14 days

Alternative oral regimens for these 3 drugs should the subject be able to transition to an oral regimen to complete the 14 days of therapy are as follows:

Ampicillin 500 mg orally every 6 hours (or alternative beta-lactam antibiotic) for 14 days or  
Clindamycin 300 mg orally every 8 hours for 14 days or  
Moxifloxacin 400 mg orally once a day for 14 days

At the conclusion of therapy for invasive disease, we will obtain throat and stool cultures to determine whether the subject is colonized with LGG in either of these locations. The *in vitro* susceptibility pattern of the isolate will be rechecked to guide additional antibiotic therapy to eradicate the LGG. Subjects will be followed until LGG is no longer isolated from these potential colonizing sites.

## 9.7 Safety Oversight and Study Termination

NIH or the Principal Investigator will appoint a Data and Safety Monitoring Board (DSMB). The DSMB is responsible for monitoring the project for subject safety and adequacy of data quality. The DSMB will advise the Principal Investigator. If the DSMB recommends a study change for subject safety or ethical reasons, or if the study is closed early due to slow accrual, the Principal Investigator will be responsible for implementing the recommendations as expeditiously as possible, according to standard policies of NIH. If the PI does not concur with the recommendations of the DSMB, the NIH program office, Principal Investigator, and DSMB chair will be responsible for reaching a mutually acceptable decision according to usual practices. The DSMB will meet approximately every 6 months (either in person or by conference call) during the study and more frequently as needed. The DSMB will consist of at least 3 members: two physicians (at least one infectious disease specialist) and a statistician. Decisions will be made by majority vote. The DSMB members will receive reports of all Grade 1-4 toxicities throughout the conduct of the study. The DSMB will make recommendations to the PI based on their analysis of the reports.

The study may be terminated at any time, including at a DSMB interim safety review. If a Grade 4 or serious AE occurs (see Appendix A and Section 9.4.1.1) and the event is judged to be probably or definitely related to having received the study drug, the study will be immediately suspended by the Principal Investigator pending review of all appropriate safety data. The event will be reported to the DSMB, IRB and FDA within 72 hours of notification of its occurrence. No additional subjects will receive the study drug depending on the joint decision of the DSMB and Principal Investigator as to whether further doses can be given or the entire trial should be terminated.

DSMB members will be asked to review our assessment of the likely relatedness of the Grade 4 or SAE to the study drug, and if it is considered probably or definitely related, the event will be considered an SAE that will result in stopping of the study.

## **10 CLINICAL MONITORING**

### **10.1 Study Monitoring Plan**

The CRCs in both institutions have procedures in place to verify consent and HIPAA requirements at each visit. During the study, the FDA may monitor the clinical site at its discretion to check the progress of enrollment, verify the presence of informed consent and HIPAA authorization, check adherence to the inclusion/exclusion criteria, monitor completeness of study subjects' records and accuracy of entries on the CRFs, review adherence to the protocol and to Good Clinical Practice, verify the study drug is being stored, dispensed, and accounted for according to specification, and review documentation of serious adverse events and the recording of safety variables. The clinical monitoring plan document in the Manual of Operations will include details describing who will conduct the monitoring, at what frequency monitoring will be done, and what level of detail monitoring will be conducted (the number of subject charts to be reviewed, which/what proportion of data fields will be monitored, and what will be monitored), and who will be responsible for ensuring that monitoring findings are addressed. No information in these records about the identity of the study subject will leave the clinical study site.

## **11 STATISTICAL METHODS**

### **11.1 Sample Size Considerations**

The sample size for this study is not determined from power analysis. The sample size of 10-15 adults was recommended by the FDA.

### **11.2 Interim Analysis**

There are no formal statistical interim analyses for this Phase I study. Interim safety data will be provided to the DSMB approximately every 6 months.

### **11.3 Statistical Analysis**

#### **11.3.1 Safety**

Adverse events reported by subjects who receive at least one dose of the study will be summarized by body system and relationship to study product. The rate of Grade II or higher vital signs, physical examinations and laboratory tests will be calculated and summarized using descriptive statistics. Concomitant medications and significant non-drug therapies will also be reported. The precise type of missing data, should it occur, will be described.

#### **11.3.2 Microbiota Richness and Diversity**

Richness will be reported as the number of operational taxonomic units. Diversity will be reported as the Shannon Diversity Index. Additional graphical output such as heat maps will be generated.

#### **11.3.3 Cytokine Production**

We will describe the time course of mRNA production of TNF- $\alpha$ , IL-12, IL-6, IFN $\gamma$ , IL-10) and different Mitogen activated protein kinase (MAPK)p38, phosphatidylinositol 3 (PI3) kinase, and nuclear factor Kappa B (NF-KB), over time.

## **12 SOURCE DOCUMENTS AND ACCESS TO SOURCE DATA/DOCUMENTS**

Medical and research records will be maintained for this study in compliance with ICH E6, Section 4.9, and regulatory and institutional requirements for the protection of confidentiality of research subjects. Study staff listed in the consent form will have access to records. Authorized representatives of NIH and regulatory agencies may examine (and when required by applicable law, to copy) clinical records for the purposes of quality assurance reviews, audits, and evaluation of the study safety and progress.

Source documents for this study contain demographic and medical information, and a copy of the signed Informed Consent /HIPAA Authorization. Clinical lab test results will also be the source documents for this study.

## 13 QUALITY CONTROL AND QUALITY ASSURANCE

The quality of the research will be assured by the following:

- Developing Standard Operating Procedures (SOPs) that detail how the research team will ensure that data are generated, documented, and reported in compliance with the protocol, GCP, and the applicable regulatory requirements (refer to Section 10). These will include:
  - Accountability procedures for the study drug to clearly outline responsibilities and expectations (Refer to Section 6.3)
  - Procedures for ensuring that the study drug being used contains the appropriate amount of active LGG throughout the study.
  - A study schedule and study procedures to clearly outline what happens at each stage of the study (Refer to Section 7 and Section 8)
  - A plan to evaluate safety which includes safety parameters to be evaluated and methods and timing for assessing and recording safety data (Refer to Section 9)
  - Internal site monitoring procedures to identify problems quickly so they can be resolved and prevented from occurring in the future
  - Data handling/record keeping procedures to clearly outline how data are recorded, who is responsible for various data management tasks, how often summary reports are written, how protocol deviations are handled (Refer to Section 15)
    - Applying quality control to each stage of data handling to ensure that all data are reliable and have been processed correctly (Refer to Section 15)
    - Appointing a Data Safety Monitoring Board to assess the progress of the trial, including safety data (Refer to Section 9.7)
    - Developing a training program for study staff to ensure that each member of the study team has the knowledge base to effectively/accurately carry out study responsibilities

## **14 ETHICS/PROTECTION OF HUMAN SUBJECTS**

### **14.1 Ethical Standard**

The investigator will ensure that this study is conducted in full conformity with the principles set forth in The Belmont Report: Ethical Principles and Guidelines for the Protection of Human Subjects of Research of the US National Commission for the Protection of Human Subjects of Biomedical and Behavioral Research (April 18, 1979) and codified in 45 CFR Part 46 and/or the ICH E6; 62 Federal Regulations 25691 (1997).

### **14.2 Institutional Review Board**

Before implementing this study, the protocol, the proposed Informed Consent/HIPAA Authorization, and other information to study subjects must be reviewed by the Institutional Review Board (IRB). A signed and dated statement that the protocol and Informed Consent/HIPAA authorization have been approved by the IRB must be obtained before study initiation. Any amendments to the protocol which need formal approval as required by federal law will be approved by this committee. The IRB will also be notified for all other amendments (i.e. administrative changes).

### **14.3 Informed Consent Process**

Informed consent is a process that is initiated prior to the subject agreeing to participate in the study and continuing throughout the subject's study participation. Extensive discussion of risks and possible benefits of this therapy will be provided to the subjects and their families. Consent forms describing in detail the study drug, study procedures, and risks are given to the subject and written documentation of informed consent is required prior to administering study drug. Consent forms will be IRB-approved and the subject will be asked to read and review the document. Upon reviewing the document, the investigator will explain the research study to the subject and answer any questions that may arise. The subjects will sign the informed consent document prior to any procedures being done specifically for the study. The subjects should have the opportunity to discuss the study with their surrogates or think about it prior to agreeing to participate. The subjects may withdraw consent at any time throughout the course of the trial. A copy of the informed consent document will be given to the subjects for their records. The rights and welfare of the subjects will be protected by emphasizing to them that the quality of their medical care will not be adversely affected if they decline to participate in this study.

In addition to the research consent form, a consent form for HIV testing will also be used in this study. This HIV testing consent form has been approved by Tufts Medical Center or Massachusetts General Hospital.

This study includes an optional sub-study. Subjects who enroll in the study will be given an opportunity to accept or decline participation in the optional sub-study. They are not required to participate in the sub-study.

